## Abstract

**Background:**

Fibromyalgia syndrome (FMS) is a chronic condition characterised by the presence of complex multiple symptoms, often accompanied by psychiatric comorbidities and sleep problems. The wide spectrum of symptoms and comorbid problems complicates treatment and management of the ensuing disability and symptoms. Physiotherapy approaches and mind-body practices including yoga and mindfulness are among the non-pharmacological treatment methods commonly used in FMS treatment. While there is initial evidence for these interventions, definitive conclusions about their effectiveness are still lacking and research on their combined effectiveness is limited. Therefore, this study aims to evaluate the effectiveness of a multimodal integrative protocol, the PhYoMind (PYM) intervention, which combines specific physical therapy modalities with yoga and mindfulness practices on the overall impact of fibromyalgia and functional impairment.

**Methods and analysis:**

This monocentric study uses a parallel-group (1:1) randomised controlled design, in which the outcome assessor and statistician are blinded to group allocation. Individuals with a clinical diagnosis of FMS (n=40) will be included in the study (Cohen’s f=0.675; α=0.05; power=0.80). Participants will be randomised to receive either PYM intervention in addition to Home Exercise (HE) programme or HE programme alone. The intervention period for both groups will last 8 weeks; PYM sessions will be held twice a week for 75 min each. The primary outcome is the broad disease impact and functional impairments measured by the total score of the Fibromyalgia Impact Questionnaire. Secondary outcomes include central sensitivity, as assessed by the Central Sensitisation Index; autonomic nervous system function, as measured objectively by heart rate variability; pain perception (current, average, worst), as assessed by the Visual Analogue Scale; fatigue, as assessed by the Multidimensional Fatigue Inventory; stress, as assessed by the Perceived Stress Scale; and sleep quality as assessed by the Pittsburgh Sleep Quality Index. Adherence and adverse events will be assessed for both interventions. Repeated measures ANOVA will be used to analyse the effect of time, intervention group and their interaction on primary and secondary outcomes under an intention-to-treat principle.

**Ethics and dissemination:**

Ethics approval was granted from the Ethics Committee at the Medical Faculty of Eberhard Karls Tuebingen University and at the University Hospital of Tuebingen (260/2025BO2) on 30 April 2025. The trial will be conducted in accordance with the updated principles of the Declaration of Helsinki. The study’s findings will be disseminated and documented in a peer-reviewed publication, adhering to the Consolidated Standards of Reporting Trials guidelines. After completion of the study and publication of the results, participants who are interested will be offered a brief summary of the aggregated study findings.

**Trial registration number:**

NCT07145788.

STRENGTHS AND LIMITATIONS OF THIS STUDYThis study addresses a crucial evidence gap by evaluating an innovative, multimodal, integrative intervention that combines specific physiotherapy techniques with yoga and mindfulness in patients with fibromyalgia syndrome (PhYoMind), with the aim of addressing various relevant domains of the condition.By comparing PhYoMind intervention plus home exercise with home exercise alone, the study may help clarify whether the combined intervention provides incremental benefits beyond exercise alone, thereby informing future research on complementary, non-pharmacological interventions for fibromyalgia syndrome.The follow-up period is limited to 8 weeks in this study, which limits the ability to draw conclusions regarding the long-term sustainability of the treatment effects.

## Introduction

 Fibromyalgia syndrome (FMS) is a chronic condition characterised by widespread and persistent non-inflammatory musculoskeletal pain, morning stiffness, fatigue, sleep disturbances, depression, anxiety, cognitive and emotional dysfunctions, and abnormalities in the central and autonomic nervous system.^1^,^4^ Although the etiopathogenesis of FMS has not been fully elucidated, genetic, neurological, psychological, sleep-related and immunological factors have been proposed as contributing factors.^5^ The worldwide prevalence of FMS ranges between 2 and 8%, depending on the diagnostic criteria used, and FMS is more common in women than in men.^6 7^ Abnormal functional neuroimaging of individuals with FMS shows that the central nervous system (CNS) is affected.^8^ Dysfunction in pain processing areas such as the insula, increased concentrations of pronociceptive neurotransmitters (eg, substance P and glutamate) in cerebrospinal fluid, dopamine dysregulation and decreased serotonin and norepinephrine in descending anti-nociceptive pathways all support CNS involvement.^8^,^10^ However, some symptoms of FMS cannot be explained solely by CNS abnormalities.^11^ They are also linked to the autonomic nervous system (ANS), including the hypothalamo-pituitary-adrenal (HPA) axis^11 12^ dysfunction. Multiple comorbidities and accompanying symptoms, in particular chronic fatigue, depression, anxiety, sleep and cognitive dysfunctions,^4 13 14^ can be explained by ANS dysfunction,^15^ suggesting that altered allostatic regulation contributes to FMS beyond CNS abnormalities.^16^

Mind-body interventions (MBIs) such as mindfulness and yoga appear to modulate pain by altering attentional deployment and cognitive control mechanisms.^17 18^ They are thought to improve cognitive flexibility by enabling the person to see their emotional reactions from an objective perspective without judgement, which could alleviate FMS-related symptoms.^19 20^ MBIs can also enhance the quality of life by improving the ability to cope with pain-related psychological problems such as stress, anxiety and depression.^21^ Furthermore, allostasis has been reported as a mechanism underlying the effectiveness of MBIs in chronic pain disorders similar to FMS,^16^ where changes in HPA-axis activity and ANS function may lead to structural brain adaptations that facilitate coping with internal/external demands.^22^ Nevertheless, recent systematic reviews have found a paucity of high-quality evidence supporting MBIs, including yoga- and mindfulness-based approaches, in the management of FMS symptoms.^23 24^ Accordingly, more randomised controlled trials have been recommended to investigate the additive or synergistic effects of different exercise modalities or techniques in combination with MBIs.^25^ In addition, the German S3 guideline for FMS strongly recommends the incorporation of meditative movement therapies, including yoga, emphasising multimodal treatment programmes.^26^

In line with the National Center for Complementary and Integrative Health’s conceptualisation of integrative approaches as a coordinated multimodal care strategy,^27^ which integrates conventional and complementary methodologies, the current study proposes a multimodal integrative approach. It has been developed specifically for this trial, integrating physiotherapy techniques into a structured yoga sequence and combining them with mindfulness principles. Neuromusculoskeletal function, pain-related biopsychological mechanisms, autonomic regulation and stress-related mechanisms are targeted simultaneously. The aim is to combine physiotherapy approaches targeting pain modulation and physical function with yoga- and mindfulness-based practices that may support stress regulation, sleep and fatigue, thereby providing an integrated approach to the multidomain symptom profile of fibromyalgia. This programme, termed PhYoMind (PYM), has been developed by combining various components whose effectiveness in addressing the different mechanisms underlying specific FMS symptoms has been suggested in a number of studies. PYM integrates specific physiotherapy techniques including Proprioceptive Neuromuscular Facilitation (PNF), Nerve Gliding Exercises (NGE), Mobility Exercises (ME) and Post-Isometric Relaxation (PIR) with yoga and mindfulness. Evidence from physiotherapy research suggests that several approaches incorporated in our intervention may help prevent declines in physical function in FMS and improve symptoms such as pain, limited range of motion, balance impairments, morning stiffness and strength.^28^,^30^ For example, PNF may increase short-term range of motion via autogenic/reciprocal inhibition; while long-term mobility gains may reflect increased tolerance through pain modulation.^31^ NGE has been shown to improve pain, functional status and fatigue in FMS, possibly through inhibition of central sensitisation, improved nerve blood flow and reduced mechanical and inflammatory stress around nerves.^28^ Another randomised controlled trial (RCT) showed that both PIR and myofascial release improved cervical and low back pain, mobility and quality of life in women with FMS.^32^ Apart from the benefits these various techniques offer on their own or as part of physiotherapy programmes, they are very well suited to yoga-based practices because they can be applied gently, gradually and tailored to the individual’s tolerance under in-person instruction and supervision. This is particularly important for FMS patients, who often have limited tolerance for high-intensity exercise.^33^ Given the complex and multifactorial nature of FMS symptoms, the structure of the PYM intervention, which addresses numerous different mechanisms, and the integration of these under a single intervention framework, along with its comprehensive structure, makes it a highly innovative intervention.

There are several FMS major guidelines that can be applied in the German context; these recommend various therapeutic approaches for the different treatment of FMS, including exercise.^26 34 35^ One of these guidelines is the European Alliance of Associations for Rheumatology (EULAR) guideline, which applies to the European context and recommends different non-pharmacological treatments, such as exercise, meditative movement and mind-body therapy for FMS. In this guideline, exercise is the only non-pharmacological treatment for FMS that is strongly recommended (strong for 100% agreement) based on high-quality evidence.^34^ The EULAR explicitly highlights aerobic and strength training as effective types of exercise for FMS.^34^ In line with this, the German interdisciplinary S3 guideline on FMS emphasises the importance of exercise (aerobic, strength and flexibility) as an intervention supported by high level-evidence and a strong recommendation.^26^ Moreover, the American College of Sports Medicine (ACSM) provides guidance on exercise dosing and prescription, which has been used to evaluate the adherence of exercise interventions to recommended dosage parameters in FMS.^36 37^ To provide a more rigorous comparison in this study, the Home Exercise (HE) programme comprises all these evidence-based recommendations: aerobic, strength and stretching exercises with the recommended dosing. Both groups receive the HE programme, while the intervention group additionally participates in PYM sessions, allowing evaluation of the added benefit of PYM beyond HEs alone.

PYM intervention stands out for its unique approach to addressing FMS symptoms; this programme, in which the techniques used in physiotherapy, yoga and mindfulness components are presented as a cohesive whole rather than as discrete modules, represents a distinctive within an integrated, replicable programme. Beyond this, the fact that the intervention group carries out both PYM and HEs has the potential to yield greater synergistic benefits for the intervention group. To the best of our knowledge, no existing research has examined the effect of integrating certain physiotherapy techniques with yoga and mindfulness in FMS patients, as proposed in this study. Therefore, the primary objective of this trial is to evaluate whether an 8-week PYM intervention in addition to HEs is superior to HEs alone in improving fibromyalgia symptom severity and functional impact after the intervention in adults with FMS. Secondary objectives are to compare the effects of the PYM and HE combination on central sensitivity, autonomic nervous system function, pain perception, perceived stress, fatigue and sleep quality with those of HEs alone. Furthermore, the study aims to monitor adverse events to assess the safety of both interventions and evaluate adherence and attendance as feasibility outcomes.

## Methods and design

This protocol for the randomised controlled clinical trial has been reported in accordance with the most recent 2025 revision of the SPIRIT statement.^38^ The study is currently being conducted, and participant recruitment has commenced.

### Study design

This monocentric study uses a superiority randomised controlled design with parallel allocation, comparing two groups in a 1:1 ratio with both the outcome assessors and the statisticians performing the data analysis blinded to group allocation.

### Study settings and recruitment

Potential participants will be recruited from the greater Stuttgart area through external channels (eg, social media campaigns, flyers, outpatient clinics, FMS self-help groups in Stuttgart, community advertising). Advertising activities will be supported by the communication department of the research centre. In addition, the study will be presented in person to local FMS self-help groups by members of the study team. The trial will be conducted at the Bosch Health Campus, Stuttgart, Germany and interventions are planned to be carried out between March and July 2026.

### Eligibility criteria

Interested individuals who have become aware of the study through the aforementioned channels will contact the study team by phone or e-mail. A telephone pre-screening procedure is conducted to determine the likely presence of FMS based on a recognised diagnosis and current symptoms. If the pre-screening yields positive results, interested patients will be invited to the Bosch Health Campus, where eligibility will then be assessed by detailed clinical examination, including confirmation of the fibromyalgia diagnosis^39 40^ and verification of all inclusion and exclusion criteria by the study physician.

The following inclusion and exclusion criteria are defined for participation:

Inclusion criteria:

Age ≥18 years.Clinically diagnosed FMS (it will be confirmed using the 2016 American College of Rheumatology (ACR) diagnostic criteria,^40^ which incorporate the severity of symptoms and require the presence of widespread pain. These criteria are the most current, widely used in both clinical and research contexts).

Exclusion criteria:

Other serious illnesses causing severe pain and complicating participation in the study.Receiving another physiotherapy treatment concurrently with this study.Regular practice of yoga and/or mindfulness exercises prior to the study.History of acute myocardial infarction or heart failure and resulting cardiac capacity limitations.Uncontrolled hypertension (resting systolic/diastolic blood pressure ≥160/100 mm Hg).Current treatment with medications known to significantly affect heart rate variability (HRV) (eg, beta-blockers or antiarrhythmic drugs).Pregnancy or planned pregnancy during the study period.Severe psychiatric disorders or insufficient cognitive abilities resulting in inability to participate in the study.Participants must either be on a stable treatment for FMS or not receiving any treatment, with no intention to alter their treatment plan during the study period. (Any unintended changes in fibromyalgia-related medications or other treatments during the study will be recorded and documented).

Eligible patients will be included in the study and will sign the written informed consent form prior to any study procedures (see onlinesupplemental files 1  2: Patient Consent Form). Baseline measurements will be conducted on the same day. In addition, on the same appointment, all included participants will have a face-to-face session with study personnel and will be taught the HEs based on a HE brochure and will be asked to follow the prescribed HEs once the study intervention begins via email. Participants in both groups may continue their usual medical care, including ongoing FMS medication at a stable dose where possible, with no study mandated changes as well as routine primary care. However, the initiation of new treatments that could directly influence the trial’s outcomes, such as additional physiotherapy, structured exercise programmes or yoga- and mindfulness-based interventions, or any medication changes targeting pain or fibromyalgia, should be avoided for the remainder of the study. Such cases will be documented by the study team.

### Intervention and comparator

PYM intervention will be carried out in a dedicated exercise room at Bosch Health Campus, which is equipped with the necessary materials for the sessions. PYM sessions will be conducted by the study physician ([name]), who is an orthopaedic specialist and experienced yoga instructor with 840-hour yoga teacher training. One of the authors ([name]), a physiotherapist and also a certified yoga instructor with 420-Hour yoga teacher training, will provide detailed instruction on the PYM protocol to the study physician prior to study start, and together they will define the structure and content of intervention sessions to ensure consistency, fidelity to the protocol and safe delivery of the intervention.

#### Intervention group: supervised PYM sessions+home exercise

Intervention group participants will receive both the supervised PYM intervention and an unsupervised home-exercise programme (see detailed description: Active Control Group). Participants in the intervention group will be divided into two subgroups of up to 10 participants. Each subgroup will attend 16 supervised PYM sessions over 8 weeks (two times per week, 75 min per session) and complete 16 HE sessions in the same period (two times per week, 60 min per session). This subgroup division is intended to facilitate appropriate modification of the practice to participants’ individual limitations and to allow closer observation during the PYM sessions. In addition, the intervention will be delivered in successive cohorts, with short gaps between cohorts to accommodate assessment scheduling. The sessions will follow the structure outlined in table 1, and verbal and tactile adjustments will be made if necessary.

**Table 1 T1:** PhYoMind intervention structural framework

PhYoMind intervention			
At the beginning of each session, setting an intention and inviting practice accordingly			
1.	Body tapping, full body shaking, dynamic warm-up sequences or easy sun salutations		10 min
2.	Standing poses	Physiotherapy techniques will be used in yoga poses: *Self-proprioceptive neuromuscular facilitation techniques*****, self-nerve gliding techniques**†**, self-mobility exercises**‡*	40 min
3.	Back bend-focused poses		
4.	Forward bend-focused poses		
5.	Three block poses (hip openers/strengtheners, core strengtheners, spinal rotation or balance-oriented poses)		
6.	Inversion pose (legs up the wall pose)		2 min
7.	Breathing practices (alternate/left nostril breathing and humming bee breathing)		8 min
8.	Mindfulness meditation		5 min
9.	Shavasana pose with post isometric relaxation§		10 min

* Contract-relax technique, contract-relax antagonist contract technique.

† Median nerve, ulnar nerve, radian nerve, sciatic nerve, femoral nerve gliding.

‡ Shoulder, spine and hip mobility exercises.

§ Sequential submaximal isometric contractions of major muscle groups from feet to head, followed by one whole body squeeze-release, then resting in Shavasana.

As seen in table 1, body tapping will be performed at the beginning of the session to warm up the body. Body tapping involves meridian pathways referring to acupoints, specific and anatomically standardised locations on the body in Traditional Chinese Medicine.^41^ In accordance with the WHO’s standard nomenclature, these acupoint-based meridian pathways incorporate various organ meridians, including the lung, large intestine, heart, kidney and liver meridians, among others.^42^ The body tapping procedure is initiated in an upright position with feet shoulder-width apart and knees slightly bent. Gentle bouncing movements are performed while tapping and scanning all these pathways in a sequence using both hands, starting from the head and progressing to the legs, similar to the intervention procedure described by Neimeyer.^43^ The tapping sequence progresses through the top of the skull, face, chest, shoulders, arms (forearm to palm and back for each side), upper and lower abdomen, front and back, outer and inner thighs, concluding with gently full body shaking movement. Dynamic warm-up sequence or sun salutations (Surya Namaskar), modified for ease of performance, will then be performed, just as in a regular yoga session, to warm up the body. In order to ensure that participants can comfortably perform the sun salutation movements, these movements will be performed as a simplified sequence. For instance, rolling the spine up and down to move from mountain pose into a forward bend, or flowing smoothly from easy cobra pose into elbow plank pose. Then, yoga poses will be implemented in the order of a typical hatha yoga planning for 40 min. Each session will focus on different parts of the body, and yoga poses will be selected according to these focused areas, as well as the spiritual and philosophical intent of that day’s session and will be planned using the Tummee Yoga Sequencing Platform.^44^ The participants’ needs and their physical abilities will also be taken into consideration. For instance, the first session will focus on the hip region and lower extremities, the second session on the upper body and upper extremities, the third session on the core and anterior myofascial line, and the fourth session on the back and posterior myofascial line. These focus areas will then be repeated in the similar sequence until the final week. An example of a PYM session is described in detail in online supplemental file 3 (Example PhYoMind session).

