### Sample size estimation

Sample size was estimated using G*Power (V.3.1.9.7; Franz Foul, University of Kiel, Germany). The sample size was calculated based on a Repeated Measures Analysis of Variance (ANOVA), according to effect estimates from previous studies using our primary outcome, the Revised Fibromyalgia Impact Questionnaire.^57^ A minimum total number of participants of 32 is required to achieve 95% power with a type I error of α=0.05, for an expected effect size f=0.675 (d=1.35). Taking into account an expected dropout rate of 20%, the required sample size for our study is 40 participants, with 20 individuals per group.

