### Statistical analysis

The data obtained during the study will be analysed using the statistical software R, V.R-4.3.3 for Windows. Descriptive statistics including mean, SD, median, etc, will be calculated for demographic and clinical characteristics in both groups. Repeated Measures ANOVA (rmANOVA) will be used to analyse the effect of time, intervention group and their interaction on primary and secondary outcomes. Time will be considered as the within-subject factor and group will be considered as the between-subject factor. Effect sizes and group differences will be reported subsequently. The significance level will be p<0.05.

To ensure the robustness and validity of the statistical analysis, missing data will be addressed using multiple imputation. All randomised participants will be included in the main analyses according to the intention-to-treat principle and will be analysed in the groups to which they were originally allocated. Serious and non-serious adverse events and drop-outs during the intervention period will be summarised and compared between groups using absolute and relative frequencies. Given the relatively limited sample size, no formal mediation analysis is planned as part of the confirmatory or secondary statistical analyses. Associations between fibromyalgia severity, perceived stress and clinical outcomes may be explored descriptively or in exploratory regression models, but these analyses will be considered hypothesis-generating and interpreted with caution. No formal interim analyses are planned, and no predefined stopping rules for efficacy or futility have been established.

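### PYM is taught in classes and controls exercise alone, but the stated model and sample size treat all participants as independent; if FIQ changes correlate within class, the primary standard error is too small

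*Protocol article*

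**What the plan says.** The section on the intervention group states that "Participants in the intervention group will be divided into two subgroups of up to 10 participants". Each subgroup attends 16 supervised sessions over 8 weeks. The same section adds that "the intervention will be delivered in successive cohorts, with short gaps between cohorts to accommodate assessment scheduling", but does not say how subgroups map to cohorts. The section on the active control group has those participants doing the home programme on their own, with no classes.

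The statistical analysis section names a repeated measures ANOVA for time, group and their interaction: "Time will be considered as the within-subject factor and group will be considered as the between-subject factor". It has no term for class.

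The sample size section gives: "A minimum total number of participants of 32 is required to achieve 95% power with a type I error of α=0.05". The effect behind this figure is f = 0.675, put there as d = 1.35. After 20% dropout, "the required sample size for our study is 40 participants, with 20 individuals per group". No design effect and no ICC appear.

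**The concern.** This is a partially nested design: participants are randomised individually, then grouped for treatment in one arm only. People in the same class share sessions, adaptations of the practice and group experience for 8 weeks, and the FIQ is a self-report from unblinded participants. Some within-class correlation is therefore plausible.

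Baseline measurement does not remove it. Baseline precedes randomisation, so a class effect can arise only afterwards. With two time points, the group-by-time test is a comparison of change scores, and a class effect on change enters that comparison directly.

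At stake are the type I error and the confidence interval width of the primary result. Under the stated model, any between-class variance in the PYM arm is missing from the error term.

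**Working it through.** **Inputs from the protocol article.** f = 0.675 (d = 1.35), α = 0.05, 95% power, N = 32, 20% dropout, N = 40 (20 per arm), PYM subgroups of up to 10, controls individual. A two-sided test is assumed because sidedness is not stated.

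**Assumed.** Class ICC of 0, 0.01, 0.05 or 0.10 for change in FIQ; normal changes with equal total variance (set to 1) in both arms.

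**1. Reproduce the plan's figure.** A two-sample t test with d = 1.35 has power 0.946 at 15 per arm and 0.9585 at 16 per arm. So N = 32, and 32/0.80 = 40. The plan's number is an ordinary calculation for independent observations, with no hidden allowance for classes. (The abstract gives power 0.80 for the same f. The t test would then need only 20 in total, so 32 belongs to 95%.)

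**2. True variance of the group difference.** With n per arm and classes of size m in the PYM arm only:

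- DE = 1 + (m−1)·ICC
- true variance = (DE + 1)/n

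**3. What the planned analysis reports on average.** The pooled sample variance in the PYM arm misses part of the class component. Its expectation is 1 − ICC·(m−1)/(n−1), so:

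- expected naive variance = [1 − ICC·(m−1)/(n−1) + 1]/n

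Example for n = 20, m = 10, ICC = 0.05:

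- DE = 1 + 9 × 0.05 = 1.45
- true variance × n = 2.45
- naive variance × n = 2 − 0.05 × 9/19 = 1.976
- SE ratio = √(2.45/1.976) = 1.11

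**4. Results.** Type I error is from 200,000 simulated trials per scenario, except the four-class figures, which come from a separate simulation of the same kind.

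| Layout | ICC | DE | True SE / naive SE | Actual type I error |
|---|---|---|---|---|
| 2 classes of 10 | 0 | 1.00 | 1.00 | 5.0% |
| | 0.01 | 1.09 | 1.02 | 5.5% |
| | 0.05 | 1.45 | 1.11 | 7.7% |
| | 0.10 | 1.90 | 1.22 | 10.5% |
| 2 classes of 8 (after 20% dropout) | 0.01 | 1.07 | 1.02 | 5.3% |
| | 0.05 | 1.35 | 1.09 | 7.1% |
| | 0.10 | 1.70 | 1.18 | 9.3% |
| 4 classes of 5 | 0.01 | 1.04 | 1.01 | 5.1% |
| | 0.05 | 1.20 | 1.05 | 6.1% |
| | 0.10 | 1.40 | 1.10 | 7.4% |

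**5. Power.** At d = 1.35 with 20 per arm, power of the planned test falls only from 0.985 (ICC 0.01) to 0.969 (ICC 0.10).

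**6. Can a class-aware test be primary?** With two classes of 10, the Satterthwaite degrees of freedom are 3.5 / 2.8 / 2.3 at ICC 0.01 / 0.05 / 0.10, and power at d = 1.35 drops to about 0.84 / 0.70 / 0.55. Two classes cannot estimate the ICC to any useful precision.

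**7. Does the proposed adjustment work?** Multiplying the PYM-arm variance by DE at the correct ICC brings simulated type I error back to about 5.0% to 5.5%.

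**The case against.** **The size rests on an assumed ICC.** This stands. A reader might infer that the standard error is certainly too small. The documents give no ICC, the error vanishes at 0, and at 0.01 it is negligible.

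**A single instructor is not a cause.** This stands. One teacher for every class adds no variance between classes. Any instructor effect is confounded with the treatment, so it limits how far the result generalises but does not bias the standard error.

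**Successive cohorts are not a cause either.** This stands. The participant timeline section describes the two-cohort design for participants in general, not for PYM alone. A calendar effect shared by both arms largely cancels in the group difference. With shared cohort variance of 5% / 10% and no class effect, simulated type I error is 4.8% / 4.6%, slightly conservative.

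**A cohort covariate would not repair class clustering.** This stands. If the two classes are the two cohorts, type I error with the covariate is 7.8% / 10.8% at ICC 0.05 / 0.10, against 7.7% / 10.6% without it.

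**Two classes of 10 is the worst layout.** This stands in part. Two subgroups within each of two cohorts would give four classes of about 5 and a smaller error, which the table shows.

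**Classes could be treated as fixed.** Class variance would then not belong in the error term. But the stated objective is whether PYM plus home exercise is superior in adults with FMS, not in these particular classes.

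**An SAP that is not shown may deal with this.** It may add a sensitivity analysis. The point, however, concerns what the article itself fixes: a named model with named factors, and a sample size derived under independence.

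**Conclusion.** The point holds in conditional form. The stated analysis and sample size ignore class membership in the PYM arm, so under any positive within-class correlation of FIQ change the primary standard error and confidence interval are too narrow. For ICC 0.01 to 0.10, actual type I error is about 5.5% to 10.5% with two classes of 10 and about 5.1% to 7.4% with four classes of 5. These figures assume normal changes, equal variances and equal class sizes.

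A reader might also infer that the trial is underpowered. The calculations do not support that: under the planned test, power at the assumed d = 1.35 hardly moves. The harm is to the error rate and the interval width. A correction of the primary model is not realistic with so few classes, so this is a matter for a prespecified sensitivity analysis, not a flaw that invalidates the design.

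**What to change.** Record each PYM participant's class in the dataset, and state how subgroups map to cohorts. Before unblinded analysis, prespecify a sensitivity analysis of the primary FIQ comparison:

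- Multiply the PYM-arm variance by 1 + (m−1)·ICC for ICC 0.01, 0.05 and 0.10, using the actual class sizes.
- Recompute the confidence interval and p value at each value.
- Report whether the conclusion holds across the range.

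The ICC is set rather than estimated because so few classes cannot estimate it. Add one sentence to the limitations on class delivery, and say there that a single instructor restricts generalisability.

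The cost is a few lines of text and code. With equal arm variances the sensitivity interval widens by √((DE+1)/2): 2% / 11% / 20% for two classes of 10. Recruitment, sample size, delivery and the primary model stay as they are. Because class labels would reveal the PYM arm, keep them out of the coded dataset until the blinded primary analysis is done.
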